#### Patient education and a self-managed exercise therapy program

The control intervention includes patient education and a revised self-managed exercise therapy program based on Larsson et al.’s protocol [23, 27]. The patient education contains information about wrist OA pathophysiology, the rationale behind exercise treatment, self-management strategies, pain management, and activity modification principles. In addition, participants are provided with a wrist orthosis along with usage instructions. The exercise therapy program aims to improve wrist stability, protect the joint, strengthen core muscles controlling the wrist, and engage the entire arm for more proximal muscle engagement [28–30]. It starts with isometric and grip-strength exercises and then introduces resistance training with a TheraBand for the elbow and shoulder while maintaining a stable wrist position, after 2 weeks. This differs from the protocol by Larsson et al., which focused solely on the affected wrist [27]. The exercise therapy program is performed at home, twice daily for 12 weeks, with follow-up assessments by the treating physiotherapist (PT) at 2, 6, and 12 weeks. A detailed description of the education and exercise therapy program can be found in Appendix 1.1.

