##### Pain Catastrophizing Scale (PCS)

The PCS is a PROM that assesses catastrophic thinking related to pain and its potential effects on emotional and physical functioning [39]. The questionnaire comprises 13 items, each scored on a 5-point Likert scale, ranging from 0 (“Not at all”) to 4 (“All the time”). The total score can range from 0 to 52, with higher scores indicating increased levels of pain catastrophizing.

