## Data collection and management

### Plans for assessment and collection of outcomes {18a}

Baseline data including demographics are collected by the hand surgeon responsible for the participant and stored in case report forms (CRF). PROMs and objective outcomes (wrist ROM and grip strength) are collected at baseline, 3, 6, and 12 months after intervention. Data on complications and the need for additional surgery or other treatments will be retrieved from the medical records.

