## Statistical methods

### Statistical methods for primary and secondary outcomes {20a}

For descriptive analysis, categorical data is presented as frequencies and percentages, whereas ordinal or skewed data is presented as median (IQR) and normally distributed continuous variables as mean (SD). For the primary endpoint, comparison between partial wrist denervation, and the patient education and exercise therapy program, the Wilcoxon signed-rank test will be used for paired data, and the Mann–Whitney *U*-test will be applied for unpaired data when the data are non-normally distributed or ordinal.

*T*-tests will be employed for changes in continuous data that follow a normal distribution, while the chi-square test will be used for categorical data. Normality will be assessed by the Shapiro–Wilk test. Generalized estimating equations (GEE), adjusted for age, sex, pain catastrophizing, operated dominant hand, SLAC/SNAC OA classification according to Watson and Vender [3, 4], and treatment site (Stockholm or Malmö), will be used for analysis of differences between groups regarding longitudinal data with repeated measurements. A robust estimator covariances matrix will be used. The working correlation matrix is selected according to the lowest Quasi-likelihood under Independence Model Criterion (QICC), and linear models will be used for all variables. Kaplan–Meier analysis will be performed to generate survival curves and Cox regression to compare differences in survival at 12-month post-intervention. *P*-values < 0.05 are considered significant.

Statistical analyses will be conducted following the intention-to-treat (ITT) principle. A secondary per-protocol (PP) analysis will be performed as a sensitivity analysis to assess the robustness of the findings. If a participant requires additional wrist surgery during follow-up or has a major trauma or other disease affecting the included hand, analyses will be conducted according to ITT up to that event. Data collected after such an event will not be analysed.

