PRWE is chosen as the primary outcome since it is a valid and reliable outcome for wrist OA [33] that evaluates both function and pain and focuses on the patient’s perspective [31]. However, PROMs are inherently subjective and may be influenced by age, expectations, socioeconomic status, and psychological factors [46, 47]. To account for this, grip strength and range of wrist motion are included as objective secondary outcomes. Additionally, pain catastrophizing is incorporated as a covariate in the GEE model to adjust for psychological influences on outcomes.

The prevalence of wrist OA is relatively low compared to OA in other joints [48, 49]. By adopting a multicentre design involving two major hand surgery departments in Sweden, this trial has the capacity to recruit a sufficient sample within a reasonable time frame, ensuring statistical power and robust results. Another strength is the focus on two common types of wrist OA, SLAC and SNAC, rather than including a heterogenous group of OA types. This increases internal validity, as treatment outcomes may differ among various OA subtypes.

A potential challenge is treatment adherence in the exercise therapy group. Exercise-based interventions require adherence to the program over weeks or months to achieve benefits, which may be difficult for some individuals [50]. Since pain relief from exercise therapy may take 6–8 weeks [51], maintaining participant engagement is critical. To monitor and evaluate adherence, an exercise diary will be used.

A limitation is the lack of participant blinding due to the nature of the interventions. This introduces a risk of performance bias and detection bias, particularly for subjective outcomes [52]. To strengthen the study design, objective outcomes such as ROM and grip strength are included as secondary outcome measures. Assessors and data analysts will be blinded to minimize bias.

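### The adjusted GEE includes operated dominant hand, a covariate with no value in the nonsurgical control arm, and gives pain catastrophizing no time point

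*Protocol article*

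**What the plan says.** Section {20a} of the protocol article names two layers of analysis. For the primary endpoint it names rank tests, with t-tests for normally distributed changes; none of these carries covariates. It then introduces a GEE that "will be used for analysis of differences between groups regarding longitudinal data with repeated measurements". That model is "adjusted for age, sex, pain catastrophizing, operated dominant hand, SLAC/SNAC OA classification according to Watson and Vender" and treatment site, and "linear models will be used for all variables".

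The section on comparators ({6b}) describes the control treatment as nonsurgical. Section {20a} also discards data collected after any additional wrist surgery, so a control operated on later does not gain a usable value. No section redefines the hand covariate as dominance of the affected wrist. Section {17a} says that data analysts will not know the allocation.

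On pain catastrophizing, the secondary outcomes section states: "The PCS is a PROM that assesses catastrophic thinking related to pain". Section {18a} adds: "PROMs and objective outcomes (wrist ROM and grip strength) are collected at baseline, 3, 6, and 12 months after intervention". The Discussion gives the reason for the covariate: "pain catastrophizing is incorporated as a covariate in the GEE model to adjust for psychological influences on outcomes". Neither the covariate list nor the Discussion says which measurement is used.

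**The concern.** A covariate in a model comparing two arms must be defined in the same way in both, and preferably fixed before allocation. Operated dominant hand fails this as written: it can be yes only for someone who has been operated, so it is partly a copy of the treatment indicator. A programmer who follows the text must either leave it empty for about half the sample or assign the controls an artificial value.

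Pain catastrophizing raises a different question. Each participant may have up to four PCS values, and a model for repeated measurements can take either the baseline value or the concurrent one. The control programme includes "self-management strategies, pain management, and activity modification principles", and the surgery arm receives no education after the operation, so treatment could change the PCS. Adjusting for a value that treatment has changed removes part of the treatment effect from the contrast.

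At stake is the adjusted between-group comparison of the longitudinal outcomes, which bears on the secondary objectives at 3 and 12 months and on PRWE over time.

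**Working it through.** The protocol gives no figure for either covariate, so there is none to reproduce. From the documents: 70 participants per arm and a target difference of 14 PRWE points (section {14}), with higher PRWE meaning worse disability (section {12}). A benefit of surgery is therefore written as −14. Assumed, because the documents are silent: the share p of affected wrists that are dominant, the effect γ of dominance on PRWE, the PRWE slope per PCS point, and the between-arm difference in follow-up PCS.

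**Operated dominant hand left missing in controls.** A complete-case fit keeps surgical participants only. The group variable is then constant and no between-group effect can be estimated.

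**Operated dominant hand coded 0 in controls.** Write T for surgery and D for the covariate, so that D = 1 only if T = 1 and the wrist is dominant. In the model mean = b0 + b1·T + b2·D:

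- controls have mean b0;
- operated non-dominant participants have mean b0 + b1;
- so b1 compares operated non-dominant participants with all controls.

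*Precision.* Relative to a covariate coded in both arms, the ratio of standard errors is √[1/(70(1−p)) + 1/70] / √(2/70) = √[(1/(1−p) + 1)/2].

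| p (assumed) | (1/(1−p) + 1)/2 | SE ratio | Increase |
|---|---|---|---|
| 0.4 | 1.333 | 1.15 | 15% |
| 0.5 | 1.500 | 1.22 | 22% |
| 0.6 | 1.750 | 1.32 | 32% |
| 0.7 | 2.167 | 1.47 | 47% |

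*Bias.* If dominance shifts PRWE by γ in both arms, the control mean contains p·γ and the operated non-dominant mean contains none, so b1 = −14 − p·γ.

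- γ = +5: −16.5, −17.0 and −17.5 at p = 0.5, 0.6 and 0.7.
- γ = −5: −11.5, −11.0 and −10.5.
- γ = 0: no bias, only lost precision.

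*Simulation check.* Linear models at 6 months, 64 per arm, 1,500 replicates per scenario, true effect −14. For γ = +5 the coefficients were −16.40, −17.09 and −17.32; for γ = −5 they were −11.45, −11.05 and −10.47. With γ = 0 the standard error rose from 3.74 to 4.58 (p = 0.5), from 3.74 to 4.96 (0.6) and from 3.75 to 5.56 (0.7), that is by 22%, 33% and 48%. With dominance of the affected wrist coded in both arms, the estimates stayed between −13.9 and −14.2.

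**Pain catastrophizing.** If follow-up PCS is the covariate, the contrast moves by slope × between-arm PCS difference.

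- Slope 0.4 and difference 2: 0.4 × 2 = 0.8 points. Slope 0.8 and difference 5: 0.8 × 5 = 4.0 points.
- The sign depends on which arm has the lower PCS. At slope 0.8, if controls are lower by 2 points, −14 becomes −14 − 1.6 = −15.6 (simulated −15.61). If the surgery arm is lower by 2 points, it becomes −14 + 1.6 = −12.4.
- If treatment does not change PCS, or if baseline PCS is used, there is no shift.

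**The case against.** The sponsor very probably means dominance of the study hand, which would be a harmless baseline covariate. Section {20a} elsewhere speaks of the included hand for participants in general, and literal coding would defeat the planned analyst blinding. That makes the literal model unlikely to be fitted. It does not make the text right: the covariate is named, is undefined in one arm, and is not redefined anywhere.

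The case on PCS is stronger. The article does not say that follow-up values will be used. Age, sex, disease classification and site, in the same list, are all entry characteristics, and the Discussion treats psychological factors as a trait of the patient. A condensed article may leave the time point to the full plan. This stands: the PCS part is an ambiguity, not a stated error.

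Three stronger readings are tempting. A reader might infer that adjustment for PCS favours surgery because only controls receive education. The documents do not support that direction: the trial's hypothesis is greater pain reduction with denervation, and if that lowers PCS more, the shift reverses. A reader might infer that PCS would be adjusted for itself, since linear models cover all variables; that phrase fixes the form of the model, not an unchanged covariate set. And a reader might infer a threat to the primary result, but the tests named for the primary endpoint contain no covariates.

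**Conclusion.** The hand covariate is wrong as written. Followed literally, it either loses the control arm or changes what the group coefficient estimates, with a standard error about 15% to 47% larger at an assumed dominant share of 40% to 70%, and with bias only if dominance is prognostic. A yes value would also identify an operated participant to blinded analysts.

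These sizes take the treatment effect as the group coefficient at a follow-up visit. If it were read from a group-by-visit term with baseline among the repeated values, a covariate constant over time would largely cancel with complete data; the article does not say which is planned.

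The PCS wording is open rather than wrong. The 0.8 to 4.0 points are illustrative, rest wholly on an assumed slope and an assumed PCS difference, and could go either way. It does not follow that both covariates distort the treatment effect: each does so only under the conditions above, and only in the adjusted longitudinal GEE.

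**What to change.** In section {20a}, replace the two covariates with *affected (study) wrist is the dominant hand (yes/no), defined before allocation in both arms* and *baseline PCS score*. Add that when PCS is the outcome, baseline PCS enters only as its baseline value, and that no measurement taken after randomisation enters the GEE as a covariate.

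The cost is two reworded covariates and one sentence. Section {18a} has PROMs collected at baseline, which covers the PCS; the schedule by instrument is in a figure not available here. The article does not list hand dominance among the baseline items. If it is not already recorded, it can be added, and recovered for those already enrolled, at trivial cost. Recruitment is expected to run until 2027, so the wording can be settled well before the final analysis.

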The least invasive surgical option in wrist OA is partial wrist denervation, which aims to reduce articular pain by resection of sensory nerve branches that innervate the wrist joint [5]. It is used either as a primary method for analgesia or combined with proximal row carpectomy (PRC), wrist fusion, or arthroplasty. In contrast to these more extensive procedures, denervation is a minimally invasive surgical technique that preserves joint motion and does not require postoperative immobilization. Studies have shown varied results following partial wrist denervation. Case series and a non-randomized trial including 12–89 participants have reported considerable improvements in patient-reported outcomes (PROMs), pain, grip strength, or motion after resection of the anterior (AIN) or posterior (PIN) interosseous nerves [6–9] or a combined AIN and PIN denervation [5, 10–12]. Conversely, a recent study investigating AIN and PIN denervation found only modest improvements in pain and patient-reported function, with uncertain clinical significance [13]. Further, a systematic review of denervation in posttraumatic wrist OA reported no significant change in pain scores and a decreased range of motion (ROM) after surgery [14]. The long-term effects of partial wrist denervation remain uncertain, as 24–28% of patients require additional surgery within 12–18 months after treatment due to persistence or recurrence of symptoms [13, 15]. Patient education and exercise therapy are recommended as core treatments for all individuals with OA, irrespective of age or symptom severity [2, 16–18]. These treatments have primarily been assessed on individuals with knee and/or hip OA with positive effects such as reduced pain and improved function [19, 20]. For hand OA in general, there is low to moderate evidence that exercise-based rehabilitation is effective for improving pain, stiffness, hand function, and grip strength in the short term [21, 22]. For wrist OA, only 1 RCT comprising 48 participants has evaluated a neuromuscular exercise therapy program as a core treatment [23]. This study found that a neuromuscular exercise program was not superior in reducing pain or improving function compared to a range of motion training program. To our knowledge, no RCTs have compared a surgical intervention to a nonsurgical control in wrist OA, and there is no high-quality evidence supporting the effectiveness of partial wrist denervation or exercise therapy for managing wrist OA.

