#### Survival

The survival of the two treatments will be analysed at 12 months. Survival is the success of the treatment, indicated by the absence of additional surgery during the study period due to insufficient improvement or symptom recurrence. If a participant is scheduled for additional surgery, the date of enrolment on the waiting list for surgery is recorded, and survival, measured in months, will be calculated from the initiation of study treatment to that date.

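### Lowest QICC in a linear GEE can never prefer any working correlation over independence, and independence can bias the adjusted longitudinal comparison if removal after further surgery differs between arms

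*Protocol article*

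**What the plan says.** All of the following is in the protocol article.

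- **Statistical methods {20a}, selection rule.** The working correlation is "selected according to the lowest Quasi-likelihood under Independence Model Criterion (QICC), and linear models will be used for all variables". On the variance, "A robust estimator covariances matrix will be used".
- **Same section, role of GEE.** The GEE "will be used for analysis of differences between groups regarding longitudinal data with repeated measurements". Its adjustment list is age, sex, pain catastrophizing, operated dominant hand, OA classification and site. Baseline PRWE is not on it. For the primary endpoint the section names t-tests or rank tests.
- **Same section, removal of data.** After additional wrist surgery, major trauma or other disease of the hand, the participant counts only up to the event: "Data collected after such an event will not be analysed".
- **Survival, under Outcomes {12}.** Treatment success is the "absence of additional surgery during the study period due to insufficient improvement or symptom recurrence".
- **Background {6a}.** After denervation, "24–28% of patients require additional surgery within 12–18 months after treatment due to persistence or recurrence of symptoms". No rate is given for exercise.
- **Missing data {20c}.** Imputation by a cited algorithm is planned. The section does not say whether visits dropped after surgery count as missing.

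**The concern.** A selection rule should be able to return different answers on different data. With linear models for every variable, this one cannot: its best score always includes independence.

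The robust covariance does not settle the matter. It protects the standard errors under a wrong working correlation. When participants contribute different numbers of visits, however, the working correlation also changes the point estimate. Independence GEE compares, at each visit, whoever is still in the data, and makes no use of the earlier scores of those who have left. The removal rule takes out participants because they did badly. If one arm loses more of its worst participants, that arm looks better than it is at later visits. At stake is the adjusted longitudinal comparison, which bears on the 3- and 12-month objectives in Objectives {7}.

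**Working it through.** **1. The criterion.** The protocol gives no figure to reproduce. Take linear to mean identity link and normal variance. The independence quasi-likelihood is Q = −RSS/(2φ), so

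QICC = −2Q + 2p = RSS/φ + 2p.

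All candidate structures share one mean model, so p is the same for each.

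- *Common φ:* QICC ranks structures by RSS alone. Independence GEE is ordinary least squares, which minimises RSS. No structure can score lower.
- *φ re-estimated per structure:* φ = RSS/(N − p), so RSS/φ = N − p and QICC = N − p + 2p = N + p for every structure. All tie.

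**2. Numerical check of the rule.** Inputs from Sample size {14}: 140 participants, 70 per arm, SD 24. Visits: baseline, 3, 6 and 12 months. Assumed: exchangeable correlation 0.6 or AR(1) 0.7. Candidates: independence, exchangeable, AR(1), unstructured.

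- Common φ: no structure beat independence in any run, and with outcome-driven removal independence was strictly lowest in every run.
- φ per structure: spread of QICC 0.0.
- Data imputed before the GEE: exchangeable tied with independence in 300 of 300 runs.

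**3. Effect on the 12-month contrast** (surgery minus exercise, true value −14, correlation 0.6). About 26% of exercise and 13% of surgical participants are removed by 12 months (assumed).

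| Removal depends on | Independence | Exchangeable | AR(1) | Unstructured |
|---|---|---|---|---|
| last observed PRWE (500 runs, Monte Carlo SE 0.2) | +2.5 | +0.2 | +0.8 | +0.4 |
| current, unobserved PRWE (500 runs, SE 0.17) | +3.5 | +1.7 | +2.6 | +1.9 |
| last observed PRWE, imputed before GEE (300 runs, SE 0.27) | +0.05 | +0.05 | +0.04 | +0.05 |

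In the first row the bias under independence is 2.5/14, or about 18% of the target difference. With no treatment effect and about 26% removed in each arm, the biases were −0.06 (independence) and −0.03 (exchangeable). Completely random or covariate-driven removal also showed no material difference between structures.

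**4. Effect on the 6-month contrast**, no true effect, removal on 3-month PRWE.

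- 15–25% of exercise and 5–12% of surgical participants removed, correlation 0.6, no baseline PRWE in the model, 250 runs per scenario: bias 1.6–3.9 points under independence, 0.4–0.6 under exchangeable. False-positive rate 7–16% against about 6%. The Monte Carlo SE of such a rate is about √(0.07 × 0.93/250) = 1.6 percentage points, so the low end is not distinguishable from 6%.
- Baseline PRWE added: about 1 point against about 0.
- Removal 10–13 percentage points higher in the exercise arm: 1.3–3.2 points under independence, at most about 0.8 under exchangeable.

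**5. Change scores instead of scores.** With equal variances and correlation 0.6 between all visits, cov(Y6 − Y0, Y3) = 0.6 × 24² − 0.6 × 24² = 345.6 − 345.6 = 0. Removal driven by Y3 then does not bias the 6-month change under independence. In 3,000 runs comparing observed arm means, the bias was −0.1 to 0.1. It returned, at 0.2–1.4 points, when the 3-to-6-month correlation (0.7) exceeded the baseline-to-3-month one (0.5). For change scores exchangeable can do worse than independence, by up to 1 point, because removal depends on a score that the change-score model does not contain.

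**The case against.** The strongest case against is that the consequence depends on several things the protocol does not fix.

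- **Outcome scale.** The primary outcome is defined as change in PRWE, and step 5 shows that the bias can vanish for change scores. This stands. The GEE text does not say whether scores or changes are modelled, so the sizes apply to scores modelled across visits.
- **Imputation.** If {20c} covers the dropped visits, the structures agree. This stands too, but {20a} says those data are not analysed and neither section links the two.
- **Removal rates.** The exercise-arm rate is an assumption. The only documented rate concerns denervation: 24–28% of 70 is 16.8 to 19.6, or about 17 to 20 participants over 12–18 months. If the surgical arm loses more, the bias favours denervation.
- **The removal rule is the deeper cause.** If removal depends on PRWE that is never observed, every structure stays biased. Fixing the correlation reduces the problem but does not cure it.
- **The name of the criterion.** The spelled-out name fits QIC, whose penalty is not constant. With complete data QIC chose unstructured in 53 of 60 runs and independence in 4. With PRWE-driven removal it chose independence in 300 of 300 runs in each scenario, so reading the rule as QIC does not rescue it where it matters.

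A reader might infer that the rule always returns independence. The algebra supports only that independence is never beaten: ties occur with complete or imputed data, or with a scale estimated per structure. A reader might also infer that the primary result is at risk, but the protocol names a t-test or Mann–Whitney test for it, not the GEE.

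**Conclusion.** The selection rule is empty as written. That part is algebra and needs no assumption beyond a linear model and QICC with penalty 2p. The consequence is conditional. It requires outcome-related removal that differs between arms, PRWE scores modelled across visits, and no imputation of the dropped visits. Under those conditions independence gives roughly 1 to 4 points of bias at 6 months, against under about 1 point for exchangeable and a 14-point target. The correlations and removal rates are assumed, so the sizes are illustrative.

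The documents do not support a claim that the trial is biased against denervation. That direction needs heavier removal in the exercise arm, for which no rate is given; the opposite imbalance reverses the sign, and equal removal leaves no material difference between structures. The point concerns the adjusted longitudinal analysis and should be corrected. It does not undermine the named primary test.

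**What to change.** Delete the QICC selection sentence. Specify the working correlation in advance as exchangeable or unstructured, keeping the robust covariance, for all continuous outcomes. A linear mixed model with the same terms is an alternative. Model PRWE scores, with baseline PRWE as a repeated visit or a covariate, rather than unadjusted change scores. Do not simply replace QICC with QIC. State also whether visits dropped after additional surgery are imputed under {20c}.

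The cost is a sentence or two in the analysis text, and recruitment is expected to run to 2027. The downside is that the structure is no longer data-driven. With complete data the treatment contrast was the same under every structure in the check, so little is lost there.

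### The protocol declares intention-to-treat but excludes all data after additional wrist surgery, trauma or other hand disease, so the analysis does not estimate the declared effect

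*Protocol article*

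**What the plan says.** Everything is in the protocol article.

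- Statistical methods for primary and secondary outcomes {20a}, general principle: "Statistical analyses will be conducted following the intention-to-treat (ITT) principle".
- Same section, triggering events: "If a participant requires additional wrist surgery during follow-up or has a major trauma or other disease affecting the included hand". The consequence is that "analyses will be conducted according to ITT up to that event", followed by "Data collected after such an event will not be analysed".
- Survival: success of a treatment is "indicated by the absence of additional surgery during the study period due to insufficient improvement or symptom recurrence". This is compared between arms at 12 months.
- Background and rationale {6a}, on earlier denervation studies: "24–28% of patients require additional surgery within 12–18 months after treatment due to persistence or recurrence of symptoms".
- Outcomes {12} and section {18a}: the primary outcome is change in PRWE at 6 months, and patient-reported outcomes are collected at baseline, 3, 6 and 12 months.
- Section {20c}: missing data will be imputed by a cited algorithm. It does not say whether values excluded under {20a} count as missing.

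**The concern.** ITT keeps the outcomes of randomised participants in their allocated arm whatever happens afterwards. The rule in {20a} does the opposite: it discards observed outcomes because of something that happened after randomisation. It is a fixed rule, not a detail left open for an analysis plan.

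The main triggering event is not neutral. The Survival section ties additional surgery to insufficient improvement or recurrence, so the excluded values come mostly from poor responders. That section also compares the event between arms, so the protocol allows that its frequency may differ by treatment. Removing poor responders improves the mean of whichever arm loses more of them.

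At stake is what the trial's headline result means. The Discussion says that denervation should not be considered if it is not superior. That conclusion needs a comparison of everyone randomised, including those whose treatment failed.

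**Working it through.** **1. How many participants could be affected by 6 months?** The only documented rate is 24–28% within 12–18 months after denervation. Assuming a constant hazard, the share by 6 months is 1 − (1 − p)^(6/T):

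- lowest: p = 0.24, T = 18: 1 − 0.76^(1/3) = 8.7%
- highest: p = 0.28, T = 12: 1 − 0.72^(1/2) = 15.1%

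This gives about 9–15% after denervation. No rate is given for the control arm, so a range has to be assumed.

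**2. Bias if the excluded values are dropped.** Let f be the share of an arm with an event before 6 months, and g the amount by which their PRWE improvement falls short of the others'. The mean of the whole arm is the mean of the non-failures minus f·g, so dropping failures raises the arm's mean improvement by f·g. For denervation (D) minus control (C):

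bias = fD·gD − fC·gC

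With a common g this is g·(fD − fC). At 12% versus 5%, g = 14 gives 14 × 0.07 = 0.98 points and g = 24 gives 24 × 0.07 = 1.68 points.

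**3. Simulation.** There were 400,000 participants per arm, with PRWE at 0, 3 and 6 months normal with SD 24 (the planning SD). Assumed correlations were 0.5 (0 with 3 months), 0.5 (0 with 6) and 0.7 (3 with 6). The true difference was 14. The chance of additional surgery depended on the 0–3-month change (logistic slope 0.04 or 0.08 per point) and was calibrated to the failure share. The surgery itself was assumed to leave PRWE unchanged. The imputed column predicts excluded 6-month values from baseline and 3-month PRWE, fitted by arm in those without an event.

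| Failures, denervation / control | Difference, values dropped (slope 0.04; 0.08) | Difference, values imputed |
|---|---|---|
| 12% / 12% | about 14; about 14 | about 14 |
| 5% / 12% | 13.0; 12.5 | about 14 |
| 12% / 5% | 15.0; 15.6 | about 14 |
| 10% / 25% | 12.0; 11.1 | about 14 |
| 25% / 10% | 16.0; 16.9 | about 14 |

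The shift is about 1 to 1.5 points at 12% versus 5% and 2 to 3 points at 25% versus 10%. Against the 14-point MCID, 1 to 1.5 points is 7–11% and 2 to 3 points is 14–21%.

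**4. Sharper selection.** If the worst 3-month responders are exactly the ones who fail (64 per arm, 3-to-6-month correlation 0.6), dropping them gives a bias of about 1.7 points at 12% versus 5% and 3.3 at 25% versus 10%. When denervation fails more and there is no true effect, type I error is 7.6% and 10.5% instead of about 5%. When control fails more, power for 14 points falls from about 0.91 to 0.81 and 0.69.

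**5. What imputation estimates.** If later surgery improves PRWE by e points, the ITT difference is the no-further-surgery difference plus (fD − fC)·e. Imputing from pre-event visits returns only the first part. With 12% versus 5% and an illustrative e of 14, the gap is 0.07 × 14 = 0.98 points. It is zero only if e is zero or the failure shares are equal.

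**The case against.** The strongest objection is that section {20c} plans imputation. In the simulation, imputing from the retained baseline and 3-month visits restores about 14 points in every scenario. This stands: a reader might infer that imputation cannot repair the dropped values, and under this model that is wrong. What remains is that the protocol does not say excluded values will be imputed, and that the imputed result answers a different question from ITT when further surgery changes PRWE.

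Second, an effect without further surgery can be a legitimate target. That is true, but the protocol does not name it as the target and labels the analysis ITT.

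Third, several stronger readings go further than the document.

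- A reader might infer that all treatment failures leave the PRWE comparison. Pre-event visits are kept, so at 6 months only earlier events matter.
- A reader might infer bias whenever failure rates differ. Bias also requires failures' outcomes to differ from whatever replaces them, and it can arise at equal rates if that gap differs by arm.
- A reader might take a quarter of an arm as lost. The 24–28% covers 12–18 months after denervation, so 25% by 6 months is unsupported in either arm.
- A reader might assume that controls will be offered denervation at 3 months, or that the exclusion starts at waiting-list entry. Section {17a} mentions only a discussion of further treatment options, and waiting-list dating is stated only for survival.

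The separate survival analysis reports failures but does not correct the PRWE comparison. No bias argument is made here for trauma or other hand disease; for those events the point is only the conflict with ITT.

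**Conclusion.** The contradiction is explicit and nothing elsewhere in the protocol withdraws it. ITT is declared, and data after an outcome-related event are then excluded. The rule should be changed before the final analysis.

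The numerical effect on the 6-month result is modest at plausible rates: about 1 to 1.5 points at 12% versus 5% if values are dropped. It reaches 2 to 3 points only at 25% versus 10%, which is above what the cited figures imply. Its direction depends on which arm has more further surgery, which is unknown. Exposure is greater at the secondary 12-month visit. These sizes rest on assumed control rates, correlations and selection strength, and on further surgery leaving PRWE unchanged. With imputation from pre-event visits the bias can largely vanish, but the estimate is then the effect had no further surgery occurred, not the ITT effect.

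**What to change.** Replace the last sentence of section {20a} with: *All outcome data collected from randomised participants are analysed in the allocated arm regardless of additional surgery, trauma or other disease.* Make this the primary analysis. Keep the truncated analysis as a labelled supplementary analysis that is not called ITT, and state there whether excluded values are dropped or imputed. A further sensitivity analysis scoring additional surgery as no improvement is optional.

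The cost is a change of wording. The visit schedule in {18a} makes no exception for participants who have had further surgery, but the protocol should confirm that their visits continue. No extra participants are needed: with all data kept, power is about 0.91 at 64 per arm on the stated 14 points and SD 24. The small downside is that the primary estimate then includes the effect of later surgery, which is why the supplementary analysis is worth keeping. Recruitment is expected to run until 2027, so the change can be made in time.
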